### 2.3. Eligibility Criteria

Patients must meet the following inclusion and exclusion criteria to be eligible for the study.

#### 2.3.1. Inclusion Criteria

Adults over the age of 18 years.Diagnosed with type 1 diabetes.Able to speak, read and understand Spanish.

#### 2.3.2. Exclusion Criteria

Have a terminal illness.Have at least one of the following clinical conditions or pathologies: brain injury of traumatic or hemorrhagic origin, dementia or serious mental illness such as schizophrenia.Have reading and hearing difficulties.

All participants will be required to complete written informed consent. The inclusion and exclusion criteria will be similar to those used in previous studies, following current scientific evidence in this population [4,18]. 

### 2.4. Intervention

#### 2.4.1. Diabetes Education Program

Participants randomized to the intervention group will receive a structured program of therapeutic education organized over four consecutive days. The organization of the sessions is shown in Figure 1. 

The therapeutic education will be provided by an advanced practice nurse specializing in diabetes. The sessions will be one hour a day with clear and concise information to guarantee the attention and concentration of the participants. This education program offers advanced and centralized training in diabetes care.

#### 2.4.2. Usual Care

Participants in the control group will receive the usual services offered in the endocrinology and nutrition unit of the university hospital, which include regular visits with a doctor specializing in endocrinology and with a nurse educator and standard Spanish Diabetes Society information pamphlets. Consultation care will be centralized in the pharmacological treatment regimen, dosage and guidelines.

### 2.5. Data Collection

Data collection will occur at three different time points throughout the study: at the baseline, 1 month and 3 months. The baseline visit will be in person, and subsequent visits can be either in person or over the phone. Sociodemographic data, such as gender, age, education level and employment status, will be collected at the baseline. The following parameters and scales will be collected at all three points (baseline, 1 month and 3 month).

#### 2.5.1. Blood Glucose Levels According to Continuous Glucose Monitoring Sensor

Type 1 diabetes patients in the endocrinology and nutrition unit have the opportunity to benefit from the free, hospital-funded sensor for continuous glucose monitoring. The sensor is implanted in the back of the arm; it has a microfilament that allows measuring glucose in the interstitial fluid. Patients must change their sensor every 14 days. The glucose levels can be visualized by both a specific reader and a mobile application based on near-field communication (NFC) technology.

This is an objective report on the evolution in glycemic control after receiving training in the diabetes education program. The nurse will have access to these data, and the parameters to be evaluated will be the following: times in high range (>181 mg/dL), target range (70–180 mg/dL) or low range (<69 mg/dL); average glucose (mg/dL); and glucose management indicator (%).

#### 2.5.2. General Knowledge about Diabetes Management

A brief knowledge test was administered to each patient. The test consisted of ten short questions to test their basic knowledge about diet and insulin management. This questionnaire will help us to know if the patient’s knowledge improves after participating in the therapeutic education program (Annex 1).

#### 2.5.3. Clarke Test

The perception of hypoglycemia was previously measured using the Clarke test [19], which consists of eight questions. A validated version in Spanish will be used for this study. The Spanish version of the Clarke questionnaire has good psychometric properties, and it is a useful instrument for assessing the presence of undetected hypoglycemia in patients with type 1 diabetes mellitus. The Spanish version showed a Cronbach’s coefficient for internal consistency of 0.75, a correlation coefficient for test–retest reliability of 0.81 and correlations of the questionnaire score with the frequency of non-severe and severe hypoglycemia of 0.47 and 0.77, respectively [20]. 

#### 2.5.4. Diabetes Self-Care Activities Scale

Self-care in this study will be measured using the Summary of Diabetes Self-Care Activities (SDSCA). An adapted and validated version in Spanish will be used in this study. This tool has a simple format that is easy for the patient to fill in, which is why it has been widely used in various studies. The Spanish version of the instrument is culturally appropriate, valid and reliable among Spanish patients with diabetes (Cronbach’s alpha = 0.62) [21].

#### 2.5.5. Goldberg Anxiety and Depression Scale

Emotional state will be assessed using the Goldberg Anxiety and Depression Scale. This is a simple and easy test for patients and is composed of two subscales of nine binary (yes/no) items. The whole scale presents a 91% specificity and 86% sensibility. The cut-off point for the anxiety subscale is 4 or more points, and it is 2 or more points for the depression subscale. The Cronbach’s alpha coefficient for the anxiety subscale is 0.75, and for the anxiety subscale it is 0.73. The reliability coefficient for the anxiety subscale is 0.73, and that for the depression subscale is 0.78, both of which are considered acceptable [22]. 

### 2.6. Data Analysis

All data obtained will be analyzed using the statistical tool IBM SPSS 24.0. Baseline data will be compared between groups using chi-square analysis or independent *t*-test. Parametric statistical tests will be used after checking the normal distribution of the sample. Repeated-measures analysis of covariance will be performed, and the interaction effects on each continuous outcome will be calculated. The chi-square test or Fisher’s exact test will be used to determine the differences in glycemic control and self-care between the two groups. Logistic regressions will be performed to determine the influence of the independent variables on the selected dependent variable. The level of statistical significance will be set at a p value of less than or equal to 0.05. 

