### 2.2. Population and Sample

This study is aimed at patients who came to the endocrinology and nutrition unit with a diagnosis of type 1 diabetes mellitus. Participants will be recruited during an endocrinology consultation with a medical professional specializing in diabetes. They will be recruited through random sampling at a public hospital in Spain. 

Randomization in blocks of 10 will be used (five experimental and five controls) to achieve balance in the randomization procedure. A person unrelated to the research objectives and data collection will prepare the sealed envelopes according to the generated randomization list. A unique patient ID will be assigned, and each patient will be allocated into one of the two groups. 

The sample size will be calculated based on Cohen’s (1992) recommendation for the expected differences between groups. Previous studies that examined the effect of diabetes self-management education on glycemic control and health-related self-care in patients with diabetes suggested a medium effect size. Given the medium effect size (0.5), a repeated-measures analysis of covariance will be performed to test for differences between the two groups, and approximately 176 participants will be required to achieve a 95% power at a 5% level of significance [17].

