### Limitations

Several questionnaires were selected to analyze the relevance and effectiveness of the program, but the authors made an effort to find validated scales in Spanish, preferably specific to the population with type 1 diabetes. Only one non-validated questionnaire was used to assess the degree of knowledge about the management of diabetes. The researchers found it interesting to include it to identify the training needs of the subjects and the level from which they started. 

One limitation is that possibly that the intervention addresses too many aspects of diabetes diet and self-care in just four sessions. Based on previous experiences in the education classroom of this unit, the sessions are usually well organized, and the patients understand all the knowledge addressed in four days. For this reason, people with cognitive, vision or hearing disorders will be excluded to alleviate this deviation.

For greater data blinding, the personnel who analyze the data will not be the same as those who teach the educational sessions. The nurse educators will be unaware of the study objectives; the questionnaires will be administered by the research nurse. 

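### If the education arm is taught in groups, as the classroom wording suggests, the repeated-measures ANCOVA and the 176-patient calculation ignore course clustering and understate the standard error of the arm difference

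*Protocol article*

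**What the plan says.** **Randomisation** (Protocol article, 2.2) is by individual patient, 1:1: "Randomization in blocks of 10 will be used (five experimental and five controls".

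**Education arm** (2.4.1): "Participants randomized to the intervention group will receive a structured program of therapeutic education organized over four consecutive days". On the format it adds: "The sessions will be one hour a day with clear and concise information to guarantee the attention and concentration of the participants". The section refers to Figure 1 for the organisation of the sessions. That figure is not available in the text reviewed, and no group size appears elsewhere.

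**Setting** (Limitations): the choice of four sessions is defended in these words: "Based on previous experiences in the education classroom of this unit, the sessions are usually well organized, and the patients understand all the knowledge addressed".

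**Control arm** (2.4.2): regular visits to an endocrinologist and a nurse educator, plus pamphlets. No class is mentioned.

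**Sample size** (2.2): the calculation assumes a standardised effect of 0.5 and is tied to the same type of model as in 2.6. Its result is "approximately 176 participants will be required to achieve a 95% power at a 5% level of significance". No ICC or design effect is mentioned.

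**Analysis** (2.6): "Repeated-measures analysis of covariance will be performed, and the interaction effects on each continuous outcome will be calculated". No term for the course attended is mentioned.

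**The concern.** Patients who sit through the same four-day course share its pace, its discussion and the quality of that particular delivery. Their outcomes are then likely to be more alike than those of patients on different courses. Controls have no comparable grouping, so the design would be partially nested: individually randomised, but clustered in one arm.

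A repeated-measures ANCOVA handles the correlation between visits within a patient. It does not handle correlation between patients taught together. If that correlation exists, the test rejects too often when there is no effect, confidence intervals are too narrow, and a valid test has less power than the independence calculation suggests. The primary outcome, knowledge of diet and treatment management, is the one that a shared class would shape most directly.

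**Working it through.** **Inputs from the protocol article:** total 176, so 88 per arm at 1:1; effect size d = 0.5; power 95%; significance level 5%, sidedness not stated (all from 2.2).

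**Inputs assumed:** course size m and ICC, because neither is given; clustering in the education arm only; SD = 1 in both arms.

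**1. Reproduce 176.** A two-sample t-test with independent patients has noncentrality 0.5 × √(88/2) = 3.317 on 174 degrees of freedom.
- One-sided 5%: the smallest n for 95% power is 88 per arm, total 176, with power 95.1%.
- Two-sided 5%: 105 per arm, total 210, would be needed; at 88 per arm power is 91.0%.

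So 176 matches a one-sided calculation for independent patients, with no allowance for clustering.

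**2. Variance with courses in one arm.**
- Design effect in the education arm: DE = 1 + (m − 1) × ICC.
- True standard error of the arm difference: √((DE + 1)/88), against √(2/88) under independence.
- Variance inflation of the arm difference: V = (DE + 1)/2.

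**3. Actual false-positive rate of a nominal 5% two-sided independence test:** 2 × (1 − Φ(1.96/√V)).

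**4. Power of a test that matches the design:** noncentral t with noncentrality 0.5/√((DE + 1)/88) and Satterthwaite degrees of freedom, taking 88/m courses in the education arm and 88 single patients in the control arm.

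Results at ICC 0.05:

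| m | DE | V | False-positive rate | df | Power, two-sided | Power, one-sided |
|---|---|---|---|---|---|---|
| independent | 1 | 1 | 5.0% | 174 | 91.0% | 95.1% |
| 5 | 1.20 | 1.100 | 6.2% | 49 | 87.3% | 93.0% |
| 8 | 1.35 | 1.175 | 7.1% | 28 | 84.0% | 91.0% |
| 10 | 1.45 | 1.225 | 7.7% | 21 | 81.6% | 89.5% |

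For m = 10 and ICC from 0.01 to 0.10, V runs from 1.045 to 1.45. The false-positive rate then runs from 5.5% to 10.4%, and two-sided power from 88% to 74%.

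**5. Separate the two causes.** At m = 10 and ICC 0.05, the two-sided path from 95% to 82% has two steps. The step from 95% to 91% comes from moving from a one-sided to a two-sided test, with no clustering at all. Only the step from 91% to 82% comes from clustering. At m = 5 the clustering step is 91% to 87%.

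**The case against.** **Group teaching is not stated.** The only mention of a classroom comes in a sentence about the unit's past experience, the plural nouns could simply mean the whole arm, and Figure 1 may settle the format. This stands, and it is why the point is conditional. It does not remove the point: the past experience supports the four-session format only if the trial teaches in the same way, and nothing in the article says that teaching is one-to-one. Group delivery is the more natural reading.

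**A journal article leaves model details to a fuller document.** True in general. Here, however, the article names the model and ties a specific number of patients to it, and that number reproduces without any clustering allowance.

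**Course size and ICC are invented.** They are assumptions, and the effect is modest for small courses: about 4 points of two-sided power and about 2 points one-sided at m = 5, ICC 0.05. The five education patients per randomisation block are not a class size and cannot be used as one.

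**Baseline adjustment would restore power.** Suppose 0.5 is on the raw SD scale, the baseline correlation is 0.5, and the course variance stays at 0.05. The variance of the arm difference is then (0.75 + 0.75 + 0.05(m − 1))/88. The normal approximation gives two-sided power of about 95% at m = 5 and 92% at m = 10. That weakens any claim of a firm shortfall against 95%. It does not remove the loss, because without clustering the same formula gives Φ(0.5/√(1.5/88) − 1.96) = 97%. Nor does it cure the false-positive rate. V at m = 10 becomes 1.95/1.5 = 1.30, and 2 × (1 − Φ(1.96/√1.30)) = 8.6%.

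**Stronger readings that the document does not support.** A reader might infer that the standard error is certainly too small; that needs group teaching, which is only implied, and a positive ICC, which is assumed. A reader might also charge the whole gap between 95% and the two-sided figures to clustering; about 4 points of it are sidedness. Figures for very large courses, such as 66% two-sided power at 20 per course, rest on a size that nothing in the article suggests.

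**Conclusion.** The point holds conditionally. The stated analysis and sample size make no allowance for patients being taught together, and the article's wording makes group teaching likely but not certain. Given group teaching and a positive ICC, the direction of the error is certain; its size depends on two figures that the article does not give. At an assumed ICC of 0.05 it is small with 5 per course and material with about 8 to 10 per course. The false-positive rate matters more than the power, because it bears on whether a positive result can be believed. The one-sided basis of the 95% is a separate matter.

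**What to change.** - State in 2.4.1 whether sessions are given to groups and, if so, the expected group size.
- Record the course (start date) that each education patient attends. This should be in place from the first course, because it may not be recoverable later.
- If courses are taught in groups, replace the repeated-measures ANCOVA in 2.6 with a linear mixed model for the continuous outcomes. Fixed effects: arm, visit, arm-by-visit and baseline value. Covariance: within patient across visits, plus a random intercept for course in the education arm only, with each control as a cluster of one. Use Satterthwaite or Kenward-Roger degrees of freedom. The mixed-model procedure in SPSS, the package already named, fits this structure.
- Restate the power in 2.2 for 176 patients with the expected course size and an assumed ICC, and say whether the test is one- or two-sided. The trial need not be enlarged.

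**Cost:** one recorded variable, a sentence in 2.4.1, a changed model sentence in 2.6 and a revised power statement. The downside is slightly wider confidence intervals and a lower stated power. If teaching is strictly one-to-one, a sentence saying so closes the point and no change of model is needed on this account.

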## Abstract

(1) Background: Type 1 diabetes is a chronic disease that creates a high demand and responsibility for patient self-care. Patient education, self-care training and the management of derived complications are great challenges for nurses. The objective of this project is to evaluate the efficacy of a therapeutic education program for type 1 diabetes. (2) Methods: Participants recruited to the study will be adult patients with diagnosed type 1 diabetes attending the clinic at the study site. A nurse diabetes educator will deliver a four-session education program. A two-group randomized controlled trial will be used in this study, with an intervention group and a control group. The subjects included in the experimental group will attend some health education sessions, while control group participants will receive the existing standard care provided by the endocrinology and nutrition unit of the hospital. Measurements and evaluations will be conducted at the baseline prior to the intervention and at 1 and 3 months from the intervention. (3) Conclusions: The primary outcome is improving patients’ knowledge about diet and treatment management. Secondary outcomes are improving patients’ glycemic control and mood. The findings from this study will help to determine the effect of diabetes education about self-care and treatment in patients with diabetes, as well as helping to decrease short-term and long-term complications and reduce health care costs.

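### The analysis section names only the interaction from the repeated-measures ANCOVA, without fixing the role of baseline, and puts a normality check of the sample before the parametric tests

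*Protocol article*

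**What the plan says.** The Abstract sets the aim: "The primary outcome is improving patients’ knowledge about diet and treatment management". Section 2.5.2 describes the instrument: "The test consisted of ten short questions to test their basic knowledge about diet and insulin management". Its scoring is not given there. Section 2.5 fixes the visits: "Data collection will occur at three different time points throughout the study: at the baseline, 1 month and 3 months".

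The model appears twice. In section 2.2 its purpose is a group comparison: "a repeated-measures analysis of covariance will be performed to test for differences between the two groups". In section 2.6 the only effect named from it is the interaction: "Repeated-measures analysis of covariance will be performed, and the interaction effects on each continuous outcome will be calculated". Neither section says whether the baseline score is the covariate or a level of the time factor.

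Immediately before that sentence, section 2.6 states: "Parametric statistical tests will be used after checking the normal distribution of the sample". It names no test, no object of the check other than the sample, and no alternative to the ANCOVA.

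**The concern.** The informative term in this model depends on where baseline sits.

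- **Baseline as covariate, months 1 and 3 as repeated levels.** The group-by-time interaction asks only whether the effect changes between the two visits. A benefit that is equally large at both gives an interaction of zero. The group term carries the treatment effect.
- **Baseline as one of three time levels.** The interaction does carry the treatment effect, as a 2-df test that does not say at which visit the arms differ. The group main effect is then diluted by the baseline visit.

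Section 2.6 names the interaction but leaves this choice open, so the reading could be settled after the data are seen. Neither reading yields a stated between-arm difference with a confidence interval for the primary outcome.

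The normality check raises a separate problem. ANCOVA relies on approximately normal residuals, not on a normal raw sample, and at this sample size even that matters little. A ten-question score is discrete and bounded, so a formal check of the raw score could set aside a sound analysis.

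**Working it through.** **Inputs.** From section 2.2: effect size 0.5, about 176 patients, 95% power, 5% significance, blocks of five and five, so 88 per arm. From section 2.5: baseline, 1 and 3 months. Assumed, because the article does not give them: unit SD, equal correlation r = 0.3, 0.5 or 0.7 between visits, two-sided 5% tests, complete data, and a knowledge score in whole numbers from 0 to 10.

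**Step 1: the article's own figure.** Two independent means, d = 0.5, one-sided 5%, 95% power: 2 × (1.645 + 1.645)² / 0.25 = 86.6, so 87 per arm; with the t distribution 88 per arm, or 176 in total. This reproduces the figure. Two-sided 5% needs 105 per arm (210), and 88 per arm then gives about 91% power. A two-sided baseline-adjusted comparison at one visit also gives 176 if r is about 0.39. A group-by-time interaction with f = 0.25 would need only 28–76 in total (2–3 measurements, r = 0.3–0.7). So 176 fits a difference between groups, not an interaction.

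**Step 2: power formulas, n = 88 per arm.** Let d₁ and d₃ be the effects at 1 and 3 months.

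- Post-baseline interaction: (d₁ − d₃) / √(4(1 − r)/n).
- Three-level interaction, 2 df: λ = (n/2) × Σ(d_t − mean d)² / (1 − r), with d = 0 at baseline.
- Adjusted average: [(d₁ + d₃)/2] / √(2v/n), where v = (1 + r)/2 − r².
- Adjusted 3-month difference: d₃ / √(2(1 − r²)/n).

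Sustained effect, d₁ = d₃ = 0.5:

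- Post-baseline interaction: the numerator is 0, so power is 5% at any sample size.
- Three-level interaction: Σ(d_t − mean d)² = 1/6, so λ = 7.33/(1 − r) = 10.5, 14.7, 24.4.
- Adjusted average: v = 0.56, 0.50, 0.36, so the noncentrality is 4.43, 4.69, 5.53.

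Fading effect, d₁ = 0.5, d₃ = 0.25:

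- Post-baseline interaction: 1.40, 1.66, 2.14.
- Three-level interaction: Σ(d_t − mean d)² = 0.125, so λ = 5.5/(1 − r) = 7.9, 11.0, 18.3.
- Adjusted average: 3.32, 3.52, 4.15.
- Adjusted 3-month difference: 1.74, 1.92, 2.32.

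| Power at r = 0.3 / 0.5 / 0.7 | Sustained | Fading |
|---|---|---|
| Interaction, baseline as covariate | 5 / 5 / 5% | 29 / 38 / 57% |
| Interaction, baseline as time level | 83 / 94 / 99.6% | 71 / 85 / 98% |
| Adjusted 3-month difference | 93 / 97 / 99.6% | 41 / 48 / 64% |
| Adjusted average of 1 and 3 months | 99.3 / 99.7 / 99.98% | 91 / 94 / 98% |

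Simulation with 4,000 runs agrees for the rows it covered: for the sustained effect the post-baseline interaction gave 5.3 / 4.5 / 5.2% and the three-level interaction 83 / 94 / 99.6%. With baseline as a time level, the group main effect is the weaker term (87 / 77 / 69%).

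**Step 3: the normality check.** Simulated scores were binomial or beta-binomial, mean 5–8, SD about 1.2–2.9, with 500 runs per setting.

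- Raw score, n = 176: no sample passed Shapiro-Wilk or Lilliefors in any setting.
- Raw score, n = 88: 0–17% passed Shapiro-Wilk and 0–12% passed Lilliefors.
- ANCOVA residuals, n = 176, Shapiro-Wilk: about 65–94% passed at mean 5–6, 25–29% at mean 7, and 2% or fewer at mean 8.
- Type I error of the t-test on the raw score at 88 per arm: 5.2–5.5%.

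**The case against.** A reader might infer that efficacy will be judged on the interaction and that a sustained benefit would go unseen. The article does not support that. Section 2.6 says interactions will be calculated, not that they decide the result, and section 2.2 gives the model's purpose as comparing the groups. The 5% figure belongs to one reading only. Measuring every scale at three visits fits baseline as a time level at least as well, and then the interaction is a valid test with 83% power or more for a sustained effect. This objection stands, and it limits the point to what is named and left open.

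Nor is the adjusted average best in every case. If the effect were 0.5 SD at 1 month and nil at 3 months, its simulated power is 61 / 64 / 78%, against 84 / 93 / 99.7% for the three-level interaction. The average answers whether patients benefit over the follow-up; the visit-specific differences and the interaction remain useful beside it.

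On normality, the check may be graphical or applied to residuals, and either could pass. The 0–10 scoring is an assumption. The sentence on the ANCOVA is itself unconditional, and a fallback may be left to an analysis plan. What stands is that the stated object of the check, the sample, is the wrong one.

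A reader might also infer that patients with a missed visit will be dropped. The article names SPSS 24.0 but not the procedure, and missing-data handling is commonly left to an analysis plan, so no finding is made on it.

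**Conclusion.** The point holds in a limited form. Section 2.2 gives the model the task of comparing the groups, section 2.6 names only its interaction, and the role of baseline is open. For a sustained 0.5 SD effect, that choice moves the power of the named term from 5% to 83–99.6%. The adjusted average exceeds 99% throughout. For an effect fading to 0.25 SD it is at or above the three-level interaction (91 / 94 / 98% against 71 / 85 / 98%). These figures assume equal correlations of 0.3–0.7, two-sided 5% tests and 88 complete patients per arm.

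The normality check of the sample is a poor rule: applied formally to a 0–10 score it would reject in essentially all samples of 176, while the parametric comparison keeps its size.

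This should be corrected before the data are analysed. It does not invalidate the design, and the documents do not show that an effective program would be reported as ineffective.

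**What to change.** In section 2.6, state that the treatment effect on each continuous outcome is the between-arm difference averaged over 1 and 3 months, adjusted for the baseline score, with a 95% confidence interval. It comes from a model of the 1- and 3-month scores on baseline score, arm, visit and arm-by-visit. Report the difference at each visit and the interaction as secondary.

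The sponsor may prefer 3 months alone. The cost is power if the effect fades: 41 / 48 / 64% in the case above.

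Replace the normality check of the sample with inspection of the model residuals, and give a bootstrap confidence interval as a sensitivity analysis.

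The change costs a few sentences. It needs no new data, visits or patients, and the named software can be kept.

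### Glycemic control and self-care are given both a chi-square/Fisher test and a repeated-measures ANCOVA; the article gives no patient-level cut-point for the former and does not say which analysis decides

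*Protocol article*

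**What the plan says.** Section 2.6 (Data Analysis) makes two statements in succession. The first is general: "Repeated-measures analysis of covariance will be performed, and the interaction effects on each continuous outcome will be calculated". The second names particular outcomes: a chi-square or Fisher's exact "test will be used to determine the differences in glycemic control and self-care between the two groups".

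The outcomes in the second statement are defined elsewhere in the article:

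- Section 2.5.1 lists the sensor parameters: the times spent in a high, a target and a low glucose range, and "average glucose (mg/dL); and glucose management indicator" (in %).
- Section 2.5.4 measures self-care with the SDSCA, described as a scale with a Cronbach's alpha of 0.62. It names no categories.
- The only thresholds that classify patients on a planned outcome are for mood, in section 2.5.5: "The cut-off point for the anxiety subscale is 4 or more points, and it is 2 or more points for the depression subscale".

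Section 2.2 sizes the trial on the first kind of analysis: "Given the medium effect size (0.5), a repeated-measures analysis of covariance will be performed to test for differences between the two groups". It takes the effect size from earlier studies of glycemic control and self-care, and arrives at about 176 participants for 95% power at a 5% level. Section 2.5 has all these measures taken at baseline, 1 month and 3 months.

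**The concern.** A chi-square or Fisher test compares proportions, so each patient must first be put into a category. The sensor values are continuous and the self-care instrument is a scale, yet no rule is given for turning either into categories. The glucose limits in section 2.5.1 sort readings within a patient. They do not sort patients.

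The same outcomes also fall under the ANCOVA sentence. Glycemic control and self-care, whose literature supplied the effect size of 0.5, are thus singled out by name for a test that differs from the one the sample size assumes. A plain two-by-two test does not adjust for the baseline value and discards information.

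Two things are at stake. The two analyses can disagree, and the article gives no rule for which one supports the conclusion. And if the categorical test decided, its power would depend heavily on a cut-point that the article does not state.

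**Working it through.** **Inputs.** From section 2.2: effect size d = 0.5, about 176 participants, 1:1 allocation in blocks of 10, so n = 88 per arm; 95% power; 5% level. The article does not state sidedness or a baseline correlation, so both are varied here. Outcomes are assumed normal, with SD 1 in each arm.

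**Step 1: reproduce the plan's figure.** For two means, power ≈ Φ(d√(n/2)/σ − z).

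- d√(n/2) = 0.5 × √44 = 3.317.
- One-sided 5%, no covariate: Φ(3.317 − 1.645) = Φ(1.672) = 95.3%; 95.1% with the noncentral t. The t-based sample size is 88 per arm, or 176.
- Two-sided 5%, no covariate: Φ(3.317 − 1.960) = Φ(1.357) = 91.3%; 91.0% with the noncentral t. The sample size for 95% would be 208 (normal) or 210 (t).
- Two-sided ANCOVA on one follow-up value, σ = √(1 − ρ²), assumed ρ = 0.4: Φ(3.317/0.917 − 1.960) = Φ(1.659) = 95.1%, and the required total is 176.

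The stated 176 is therefore reproducible, as a one-sided t-test or as a two-sided ANCOVA with ρ = 0.4. Either way it belongs to an analysis of means.

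**Step 2: ANCOVA over a range of assumed correlations (two-sided 5%, 88 per arm).**

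- ρ = 0.3: 93.5% (93.3% with t)
- ρ = 0.4: 95.1% (94.9% with t)
- ρ = 0.5: 96.9% (96.8% with t)

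**Step 3: the same data dichotomised.** A cut c that leaves a proportion p₁ of controls above it leaves p₂ = 1 − Φ(c − 0.5) of the intervention arm above it. With p̄ the mean of p₁ and p₂,

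power ≈ Φ( [ |p₂ − p₁| − z√(2p̄(1 − p̄)/n) ] / √{[p₁(1 − p₁) + p₂(1 − p₂)]/n} ).

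For the cut midway between the two means, p₁ = 0.401, p₂ = 0.599 and p̄ = 0.5. The two standard errors are 0.0754 and 0.0739, so power = Φ((0.1974 − 1.960 × 0.0754)/0.0739) = Φ(0.672) = 74.9%.

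| Control vs intervention above the cut | Power, two-sided 5% |
|---|---|
| 10% vs 21.7% | 56.8% |
| 20% vs 36.6% | 69.1% |
| 40.1% vs 59.9% (midway, the best of those tried) | 74.9% |
| 50% vs 69.1% (control median) | 73.9% |
| 80% vs 91.0% | 54.7% |
| 90% vs 96.3% | 37.4% |

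Exact enumeration gives 76.2% for chi-square and 72.5% for Fisher at the midway cut, and 75.3% and 70.1% at the control median.

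**Step 4: the one-sided reading.** At one-sided 5% the dichotomised power is 83.2% at the control median. At the midway cut it is Φ((0.1974 − 1.645 × 0.0754)/0.0739) = 84.0%. The t-test has 95.1%.

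**Step 5: in patients.** For 95% power at two-sided 5%, the dichotomised comparison needs 328 in total (midway cut) or 336 (control median). The unadjusted comparison of means needs 208. The ratio 208/328 = 0.63 means that even the best cut is worth about 63% of the sample.

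**The case against.** The strongest defence is that the two sentences complement each other: ANCOVA for the continuous values, chi-square or Fisher for some categorised status, then the logistic regressions that section 2.6 also mentions. Publishing both forms is common. The article is condensed, and a responder definition may well stand in a full protocol or analysis plan that is not shown. Glycemic control is a secondary outcome, and the abstract does not rank self-care at all. The SDSCA scoring is not described, so treating it as a quantitative score is a natural reading rather than a stated fact.

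Much of this stands, and it rules out some stronger readings that a reader might infer:

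- *That the plan ignores the baseline.* It does not. The ANCOVA sentence covers each continuous outcome. Only the named categorical test is unadjusted.
- *That power is in fact cut to about 75%.* This follows only if chi-square or Fisher is the deciding test, which the article does not say. Under a one-sided test the figure is about 84%.
- *That the cut-point will be picked after the data are seen.* The article gives none, but that does not show that none has been fixed elsewhere.
- *That the trial's main conclusion is at risk.* The primary outcome is knowledge, which the chi-square sentence does not mention.

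The ambiguity itself remains. The article does not merely leave the method for these outcomes to another document. It names one by outcome, and that method does not match how the outcomes are measured or how the trial was sized. If categorised versions were meant as a supplement, the sentence does not say so.

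**Conclusion.** The point holds as an unresolved conflict between two analyses of the same outcomes. The one attached to them by name is the less efficient one and has no patient-level cut-point in the article.

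The size is conditional. If chi-square or Fisher decided, with d = 0.5, 88 per arm, normal outcomes and no dropout, power at two-sided 5% would be at most about 75% (76% by exact chi-square), and well below that at uneven cuts. A t-test would have 91%, and ANCOVA about 93–97% at assumed baseline correlations of 0.3–0.5. At one-sided 5% it would be about 84% at most, against 95%. The correlations and the sidedness are assumptions, because the article states neither.

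This should be fixed, but it is not critical: it touches glycemic control and self-care only, and leaves the primary outcome, knowledge, as it is.

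**What to change.** Replace the chi-square/Fisher sentence in section 2.6 with wording such as:

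*The sensor measures (times in high, target and low range, average glucose, glucose management indicator) and the SDSCA scores will be compared between arms as continuous variables. The baseline-adjusted repeated-measures ANCOVA is the deciding analysis. Where the normality check fails, for example for time in low range, a transformation or a non-parametric alternative will be used. Chi-square or Fisher's exact tests will be used for categorical variables, and for any responder definition, which will be fixed before the data are seen and treated as supportive.*

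This matches the sample-size basis in section 2.2 and the normality condition already in section 2.6. If a responder analysis is wanted, its cut-point should be written beside it. The cost is a few lines of text. No new data, visits or patients are needed.
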